### Potential benefits and risks assessment

Joint distraction is a fairly new treatment for CMC1 OA. Patients will be informed that this treatment is not offered in regular clinical practice yet, only in the context of a formal clinical study. By participating in the study, patients contribute to better understanding in the place of CMC1 joint distraction therapy compared to the presently available surgical alternatives, which may be beneficial to patients in the future. Rehabilitation is not expected to be longer than that of the currently available invasive operative interventions.

#### Potential risks or complications

Radiation burden. A total of eight radiographs will be obtained during the study period. The radiation burden will be 0.02 mSv per radiograph, resulting in a total amount 0.16 mSv. In our opinion, this is an acceptable small amount.Pin tract infections. Based on data from the previous cohort, pin tract infections occur in approximately 1 out of 3 patients. It can usually be adequately treated with oral antibiotics. In case of persisting infection, the distractor device may need to be removed at an earlier time point. In case of severe infection, hospital admission and intravenous antibiotics may be needed, but the estimated risk is minimal.Loosening of the device due to direct external forces. A customized thermoplastic splint is fashioned directly after placement of the device to provide cover and protection. If, for any reason, the device is loosened or dislodged, re-fixation or removal will follow varying per case.Disappointing outcome. In case distraction therapy yields insufficient improvement, the established options of invasive surgical treatment will still be possible, albeit with delay caused by study participation*.*

#### Potential benefits

Patients may experience significant clinical benefits (less pain, better physical function) after this minimal invasive procedure.Patients in the 6-week group may experience less pin tract infections. A distraction period of 6 weeks has not been studied for CMC1 OA specifically, but based on knee distraction studies, 6 weeks of continuous joint distraction seems to result in less pin-tract infections compared to an 8-week distraction duration (85% versus 55% respectively) [17, 18]. However, it must be mentioned that pin tract infections occur more often during knee distraction than CMC1 joint distraction treatment [19].

### Randomization and blinding

Patients will be randomized to one of two groups at a 1:1 allocation ratio. We will use Research Electronic Data Capture (REDCap), a secure web-application and electronic platform for managing clinical research data [31], for randomization and allocation concealment. A fixed block size design will be generated in this secure web-application by the coordinating investigator who is not involved in patient care or in the assessment of the postoperative outcomes. Details about the randomization method or block sizes will not be available to or shared with those who enroll participants, assign interventions, or assess outcomes. Once a patient has been enrolled, the research assistant will log into the secured computer system (REDCap) and assign patients to group A or B. During placement of the distractor, the hand surgeon, operating room-assistant, and nurses will not know to which group the patient is randomized. Patients cannot be blinded. Radiographs will be scored by a blinded radiologist.

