### Study phases

#### Recruitment and consent

Patients visiting the plastic surgery outpatient clinic of the St. Antonius Hospital in the Netherlands due to symptoms of CMC1 OA will be screened for eligibility. A radiograph is taken at initial visit as standard of care. The hand surgeon will assess eligible patients for enrolment based on the set inclusion and exclusion criteria. Patients who fulfil the inclusion criteria will be invited to participate in the study. Written informed consent will be obtained by the coordinating investigator from all participants.

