### Data management, monitoring, and publication

Data will be handled confidentially. Data will be administered on an encrypted computer in REDCap: a secured electronic data capture tool for clinical research [31]. Patient data will be anonymized. All included patients are identified by a patient identification number. A list of these numbers with name combinations will be securely stored by the coordinating investigator. The handling of personal data will be performed in compliance with the Dutch Personal Data Protection Act and in compliance with Good Clinical Practice guidelines. Data will be kept for 15 years after the end of the study. Written informed consent from study participants will securely locked away within the hospital.

This study will be monitored by a certified monitor according to the St. Antonius Hospital and Medical Research Ethics Committees United (MEC-U) monitoring policy. Insurance is provided for all participants in accordance with Dutch legislation. The results of this study will be published in peer-reviewed journals and presented at (inter)national conferences. Any protocol amendments will be submitted at the MEC-U for approval and relevant parties, including participants, will be informed if needed.

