It is not feasible to blind participants to wearing a distractor for 6 or 8 weeks. Due to logistical constraints, we are also unable to blind surgeons and hand therapists. The lack of blinding might influence our results, but is common in trials assessing a surgical intervention. Besides, we realise the need for additional studies to compare joint distraction with other operative and non-operative techniques. However, we first designed this study to explore the possibilities to decrease distraction duration and bring CMC1 joint distraction, in this regard, in line with other joint distraction techniques. Based on the results of this current study, we will conduct a next comparative study to achieve a better understanding of the effects and benefits of joint distraction directly compared to other techniques (like splinting or trapeziectomy) in the treatment of CMC1 OA.

This study will mainly focus on clinical and patient-reported outcomes. We realise that there is also a need to gain more knowledge about the working mechanism of joint distraction. Future studies can contribute to a better understanding of this mechanism by—for example—focusing on arthroscopic sampling of articular cartilage, detailed imaging techniques, or biochemical analysis of synovial fluids.

There is major evidence that psychosocial factors—such as catastrophic thinking and symptoms of depression and anxiety—account for more of the variation in CMC1 OA symptom intensity than measure of pathophysiology [20, 21, 34]. To study differences in the magnitude of psychosocial factors before and after CMC1 joint distraction, in this study, we will measure symptoms of pain catastrophizing and of depression with two short questionnaires (PHQ-2 and PCS-4) [27, 28]. This could lead to a better understanding of the impact of psychosocial factors on physical function and other outcomes after CMC1 joint distraction therapy. Future studies can focus on exploring other/additional treatment opportunities for patients with CMC1 OA to optimize care (f.e. more effective coping strategies). This could result in a more multidisciplinary approach in treatment of CMC1 OA.

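### The role that generates the fixed-block randomisation also takes consent from every participant, so allocation concealment is not assured at the consent step

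*Protocol article*

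**What the plan says.** The Protocol article describes the path from screening to assignment in two sections.

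- *Randomization and blinding*, who builds the sequence: "A fixed block size design will be generated in this secure web-application by the coordinating investigator who is not involved in patient care".
- Same section, the safeguard: "Details about the randomization method or block sizes will not be available to or shared with those who enroll participants, assign interventions, or assess outcomes".
- Same section, the assignment: "Once a patient has been enrolled, the research assistant will log into the secured computer system (REDCap) and assign patients to group A or B".
- *Recruitment and consent*, eligibility: "The hand surgeon will assess eligible patients for enrolment based on the set inclusion and exclusion criteria".
- Same section, consent: "Written informed consent will be obtained by the coordinating investigator from all participants".

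*Data management, monitoring, and publication* adds that the coordinating investigator keeps the key linking study numbers to names: "A list of these numbers with name combinations will be securely stored by the coordinating investigator". The trial has one centre and patients are not blinded. The *Discussion* says of the clinicians: "we are also unable to blind surgeons and hand therapists". The surgeon and theatre staff are kept unaware of the group only while the device is being placed.

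**The concern.** Concealment has to hold for everyone who can influence whether and when a patient enters, until entry is irrevocable. Consent is such a step. Here the one role that necessarily knows the method and block size meets every patient at that step, while the safeguard says nobody who enrols has that knowledge. Both statements cannot be true as written.

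A person at the consent step who can anticipate the next arm could, deliberately or not, vary how participation is presented or when consent is completed. That would make the arms differ in prognosis before treatment. The primary outcome is patient-reported, and the primary analysis is described as a mean difference with its 95% CI. Selection that favoured the 6-week arm would push the result towards non-inferiority.

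**Working it through.** **1. Roles side by side**

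| Step | Who | Section |
|---|---|---|
| Generates fixed-block design | Coordinating investigator | Randomization and blinding |
| Judges eligibility | Hand surgeon | Recruitment and consent |
| Obtains consent, all patients | Coordinating investigator | Recruitment and consent |
| Makes the assignment, after enrolment | Research assistant | Randomization and blinding |
| Must not know method or block size | Those who enrol, assign or assess | Randomization and blinding |

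Rows 1 and 3 name the same role, and row 3 falls under row 5. Being uninvolved in patient care and outcome assessment, as the article says of this role, does not cover the consent conversation. Knowledge of the method and block size follows directly from row 1. Sight of the full allocation table is a natural reading, but it is not stated.

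**2. The plan's own figure**

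The article gives no figure for predictability. The sample size, used as a multiplier below, reproduces. With margin 9, SD 11, one-sided 0.025 and 90% power, n per arm = 2 × (1.960 + 1.282)² × 11² / 9² = 31.4, so 32. The total is 64, and 64 / 0.95 = 67.4, so 68. The concern does not affect it.

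**3. What the block size reveals if all earlier assignments are also known**

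Block size is not given, so 2, 4 and 6 are assumed. In a 1:1 permuted block, an assignment is certain once one arm's places are used up.

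- Block 2: the second is always certain. 1/2 = 50%, or 34 of 68.
- Block 4: the fourth is always certain; the third is certain if the first two match (probability 1/3). (1 + 1/3)/4 = 33%, or about 23 of 68.
- Block 6: the sixth is always certain; the fifth has probability 8/20 = 0.4 and the fourth 2/20 = 0.1. (1 + 0.4 + 0.1)/6 = 25%, or 17 of 68.

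A best guess at every assignment would be right 75%, 71% and 68% of the time, against 50% with no information.

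**4. Whether this extends to clinic staff**

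The first scheduled event that differs by arm is the visit at 3 weeks (group A) or 4 weeks (group B) after placement. The article expects 4 patients a month, while 68 patients over its 2 years is 68/24 = 2.8 a month. At these rates about 2 to 4 further patients enter before that visit.

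- Lag of 2 patients: blocks of 2 and 4 give 0%. In a block of 6, only the sixth can be certain, and only if the first three match: (2/20)/6 = 1.7%, about 1 of 68.
- Lag of 3 patients: 0% for all three block sizes.

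**5. Illustration of what selection could do**

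SE = 11 × √(2/32) = 2.75. Suppose 6 weeks were truly worse by the full 9 points. The chance of declaring non-inferiority is then P(Z > 1.96 − b/2.75), where b is a selection bias favouring the 6-week arm. It is 2.5% at b = 0, and about 5.5%, 11% and 19% at b = 1, 2 and 3 points. The values of b are assumptions, and nothing in the article indicates that such a bias exists.

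**The case against.** The strongest reply is that the roles are more separated than the overlap suggests. The hand surgeon decides eligibility, and a research assistant makes the assignment through REDCap only after enrolment. If those who enrol means the surgeon, the conflict narrows. This stands in part: the coordinating investigator's exposure is confined to the consent conversation and its timing. It does not remove the conflict, because consent from all participants remains part of enrolling them.

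Several stronger readings are tempting, and the article does not support them.

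- A reader might infer that the consent-taker knows every upcoming allocation. The article says this role generates a design inside a secure application. It does not say that the table stays visible to that person afterwards.
- A reader might infer that allocation was subverted. Nothing in the text shows this.
- A reader might infer that clinic staff could work out 17 to 34 of the 68 assignments. That requires every earlier assignment at once plus the block size. Staff first meet an arm-dependent visit weeks after placement, which reduces the certain share to about 0 to 2%. The research assistant does see each assignment as it is made, but is among those from whom the block size is withheld.
- A reader might take the block size as published. The article discloses only that it is fixed.
- A reader might say selection could never be detected. The planned baseline table covers PROMIS UE, MHQ, PHQ-2, PCS-4, VAS scores, strength and joint space, so imbalance in measured factors would be visible and could be adjusted for. Imbalance in unmeasured factors could not.

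The lack of blinding of patients and clinicians is a separate limitation, which the article discloses, and it concerns outcome reporting rather than concealment.

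**Conclusion.** The concern holds in a limited form. The article's concealment statement is contradicted by its own account of who takes consent. The person at the consent step certainly knows the method and block size, and may have access to the table, so concealment at that step is not assured.

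The size depends on facts the article does not give. If this person also knows all earlier assignments, the certain share is 50%, 33% or 25% for assumed blocks of 2, 4 or 6. If the table itself is visible, it could be every assignment. If the roles were separate in practice, or access ended after generation and earlier assignments were not known, the exposure is far smaller and the main need is to correct the text. The sample size and margin are unaffected.

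**What to change.** Separate the two roles for the patients still to be enrolled, in one of two ways:

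- an existing team member without access to the allocation table or block size takes consent; or
- someone without participant contact generates and uploads the remaining sequence, preferably with varied block sizes, and the coordinating investigator's access to it is removed.

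Varying the block sizes alone would reduce predictability but would not resolve the role overlap. The article names no data manager or statistician, so the sponsor would need to confirm that such a person is available before choosing the second route; the first does not require one.

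In either case, reconcile *Recruitment and consent* with *Randomization and blinding* so that they say who generates the sequence, who can see it and who takes consent. In the trial report, state how many patients were consented by the person who generated the sequence.

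The cost is a short amendment and a change of REDCap user rights, plus one table upload under the second route, with no extra patients. Patients already enrolled cannot be protected retrospectively. Recruitment was planned from 5 December 2019 to 31 December 2021 (757 days), and the article appeared on 1 May 2021 (day 513), about 68% of the way through. If recruitment has closed, only the correction of the text and the reporting remain.

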### Sample size calculation

We aim to assess non-inferiority of 6 weeks distraction compared to 8 weeks measured by PROMIS UE scores. We performed a sample size calculation based on the minimal clinically important difference (MCID) of the PROMIS UE questionnaire. The MCID is the smallest difference that patients perceive as beneficial. Previous studies report a MCID of 9.0 points for PROMIS UE with a standard deviation of 11 [32]. Non-inferiority will be considered if the mean difference with 95% confidence interval (95% CI) is no more than 9.0 points lower in the 6-week group compared to the 8-week group. To detect non-inferiority with 90% power, and a one-sided confidence level set at 97.5%, and 5% estimated loss to follow-up, we aim to include 68 patients. Each month, it is estimated that 4 patients will be eligible and willing to participate, resulting in an inclusion time of 2 years.

### Statistical analysis

The following characteristics will be reported in the baseline characteristics table: age, gender, work status, marital status, level of education, PROMIS UE scores, MHQ, PHQ-2, PCS-4, VAS for pain, satisfaction, thumb stiffness, thumb function, range of motion, strength, and joint space width on radiographs. Testing for differences in baseline characteristics among groups will only be done if visual inspection of the results indicates possible significant differences.

The primary outcome will be the difference in PROMIS UE score between the 6-week group (A) and 8-week group (B) at 1 year follow-up. We will report the mean with SD and 95% CI and the mean difference with 95% confidence interval. If the mean difference with 95% CI falls within the predefined non-inferiority margin of 9.0 points of PROMIS UE scores, we will conclude non-inferiority.

Regarding the secondary hypotheses, we will test for superiority between the 6-week and 8-week group.
We will assess any differences in MHQ scores, VAS pain, VAS satisfaction, VAS function, VAS stiffness, range of motion, and strength at 1 year follow-up compared to baseline. We will test for superiority between groups by comparing the mean differences at 1 year.Treatment failure is scored when a patient proceeds with an invasive surgical procedure (f.e. trapeziectomy) after distraction therapy due to ongoing symptoms of CMC1 OA. We will analyse the difference between groups in the proportion of participants who are classed as treatment failure at 1 year.Adverse event rates will be reported and classified according to the Clavien-Dindo classification of surgical complications. We will analyse the difference between groups in the proportion of participants who are classed as adverse event at 1 year.Joint space width at 1 year follow-up is compared to baseline measures in both groups. Mean difference in mm between groups is assessed at 1 year follow-up.

This will be intention-to-treat analyses. In case of non-adherence, to test the robustness of our results, we will also report the results of per-protocol analyses [33].

We will create 2 multivariable linear regression models to assess factors independently associated with PROMIS UE and MHQ scores at 1 year. In these models, we will include all mentioned study parameters (except PROMIS UE and MHQ scores) with *P* < 0.10 in bivariate analysis. *P* values < 0.05 are considered statistically significant.

We will perform the same statistical tests and analysis as mentioned above at 2 years and 5 years post-distraction to study the long-term results. Incomplete data will be adequately described. We will use multiple imputation for any missing data or means for missing values.

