#### Preoperative measurements

Patients will be asked to complete a series of questionnaires on REDCap, a secured web-application for clinical research, including patient demographics (gender, age, marital status, etc.), physical function, pain scores, and symptoms of depression. All questionnaires are described in detail under ‘study parameters’. Thereafter, patients will visit the hand therapist for strength and range of motion measures of both hands. Next, placement of the distraction device is scheduled and patients will be seen by the anaesthesiologist for screening and approval of the surgical procedure.

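### The primary non-inferiority comparison leaves out the baseline PROMIS UE score; adjusting for it is a nearly free gain in precision, of a size the documents do not fix

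*Protocol article*

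**What the plan says.** All references are to the protocol article.

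- **Primary comparison (Statistical analysis):** "The primary outcome will be the difference in PROMIS UE score between the 6-week group (A) and 8-week group (B) at 1 year follow-up". The reporting sentence that follows is "We will report the mean with SD and 95% CI and the mean difference with 95% confidence interval", and that interval is judged against 9.0 points. Neither sentence names a model or a covariate.
- **Baseline data:** the preoperative questionnaires cover "physical function, pain scores, and symptoms of depression" (Preoperative measurements). The baseline table is to list "age, gender, work status, marital status, level of education, PROMIS UE scores, MHQ, PHQ-2, PCS-4", among other items (Statistical analysis).
- **Baseline imbalance:** "Testing for differences in baseline characteristics among groups will only be done if visual inspection of the results indicates possible significant differences". The article does not say what would follow from such a test.
- **Secondary outcomes:** these are assessed against their baseline values ("range of motion, and strength at 1 year follow-up compared to baseline"), and then "We will test for superiority between groups by comparing the mean differences at 1 year".
- **Regression models:** two multivariable models look for factors associated with PROMIS UE and MHQ at 1 year. Their candidate predictors are all study parameters "except PROMIS UE and MHQ scores". They do not supply the non-inferiority interval.
- **Randomization and blinding:** 1:1 in fixed blocks. No stratification by baseline function is stated.

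**The concern.** In a trial of 68 patients, the baseline value of the outcome is usually the first covariate to consider. Here it is planned for every patient but does not enter the decisive comparison, although the secondary outcomes are set against their baselines.

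Two things are at stake. The first is precision: any part of the 1-year variation that baseline predicts stays in the standard error and widens the interval that is compared with the margin. The second is chance imbalance: if one arm starts with better function, part of that head start appears in the 1-year difference, in either direction. The planned response, inspection followed by a significance test, does not remove it. After randomization such a test only asks whether chance produced a difference that is already known to be due to chance.

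**Working it through.** **Inputs from the Sample size calculation section:** margin 9.0, SD 11, one-sided 2.5%, power 90%, 5% loss to follow-up, N = 68. **Assumed, not in the documents:** the correlation r between baseline and 1-year PROMIS UE, shown from 0.1 to 0.7; a baseline SD of 11; a true difference of 0.

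**Step 1. Reproduce the plan's N.** n per arm = 2 × (1.960 + 1.282)² × 11² / 9² = 31.4, so 32. Total 64; 64 / 0.95 = 67.4, so 68. This matches exactly. It uses the full SD of 11, so the trial was sized for an unadjusted comparison.

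**Step 2. Unadjusted precision.** SE = 11 × √(2/32) = 2.75. Power = Φ(9/2.75 − 1.96) = Φ(1.31) = 90.5% (89.6% with the t distribution).

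**Step 3. ANCOVA.** SE = 2.75 × √(1 − r²); power = Φ(9/SE − 1.96); half-width of the 95% interval = 2.00 × SE (t, 61 df).

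| r (assumed) | SE | Half-width | Power | Equivalent gain in patients, 1/(1 − r²) − 1 |
|---|---|---|---|---|
| unadjusted | 2.75 | 5.50 | 90.5% | – |
| 0.1 | 2.74 | 5.47 | about 91% | 1% |
| 0.3 | 2.62 | 5.25 | 92.9% | 10% |
| 0.5 | 2.38 | 4.76 | 96.6% | 33% |
| 0.7 | 1.96 | 3.93 | 99.6% | 96% |

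**Step 4. Price of the covariate.** Estimating the slope inflates the variance on average by about 1 + 1/(64 − 4) = 1.017, which the table ignores. Break-even is (1 − r²) × 61/60 = 1, so r² = 1/61 and r is about 0.13. Below that there is no gain, and the loss is at most about 1.7% of the variance.

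**Step 5. Chance imbalance.** With 34 randomized per arm, the baseline difference has SE = 11 × √(2/34) = 2.67, so its usual 95% range is ±1.96 × 2.67 = ±5.2 points. With equal SDs at both times, the expected shift in the 1-year difference is r times the imbalance:

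| r (assumed) | Shift from a 1-SE imbalance (2.67) | Shift from a 1.96-SE imbalance (5.23) |
|---|---|---|
| 0.1 | 0.3 | 0.5 |
| 0.3 | 0.8 | 1.6 |
| 0.5 | 1.3 | 2.6 |
| 0.7 | 1.9 | 3.7 |

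**Step 6. How much slack the design has.** If the SD were 13 (assumed), the unadjusted SE is 13 × 0.25 = 3.25 and power Φ(9/3.25 − 1.96) = 79%; ANCOVA at r = 0.5 has SE 3.25 × √0.75 = 2.81 and power 89%. If 6 weeks were truly 2 points worse (assumed, SD 11), power is Φ(7/2.75 − 1.96) = 72% unadjusted and Φ(7/2.38 − 1.96) = 84% with ANCOVA at r = 0.5.

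**The case against.** The strongest objection is that nothing here is an error. Under randomization the unadjusted difference is unbiased, its interval has nominal coverage, and the planned 90% power is delivered under the plan's own assumptions. All of that stands. A reader might infer that the primary analysis is biased or the trial underpowered; the documents support neither.

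A second objection is that covariates are often settled in an analysis plan or full protocol, and neither is shown. The reporting sentence would even be compatible with an adjusted difference. This lowers certainty about what will be done. But the article defines the comparison as the difference at 1 year, and its N reproduces from the full SD, so the plain reading is an unadjusted comparison.

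A third objection concerns size. A reader might suppose that a baseline imbalance passes whole into the result. It does not: only about r times the imbalance carries over, and the unadjusted standard error already allows for this variation on average. The gain also depends on an r that the documents do not give, and at low r it is negligible.

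Fourth, a reader might infer that the secondary outcomes will be compared as change scores, which at low r are noisier than ANCOVA. The wording can mean that, or a between-group difference at 1 year. No SD is given for MHQ, the VAS scales, range of motion or strength, so no loss can be calculated for them.

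Finally, no analysis or conclusion is made to depend on the baseline tests. They do little harm, but they also correct nothing. The regression models do not answer the point either: their exclusion of PROMIS UE may refer only to the outcome score, and in any case they are not the primary comparison.

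**Conclusion.** The point holds as a free improvement in efficiency, not as a fault in validity. As written, the primary comparison leaves out a baseline score that the plan collects from every patient, so it gives up precision and leaves chance imbalance uncorrected in the observed result. The benefit runs from nothing at r of about 0.1 to a standard error of 1.96 instead of 2.75 at r = 0.7. At r = 0.5 the half-width of the interval falls from 5.50 to 4.76 points. These figures rest on the plan's SD of 11, 32 evaluable patients per arm, a true difference of 0 and assumed values of r. The imbalance figures also assume a baseline SD of 11. That the baseline score is left out of the stated comparison is clear from the text; how much this costs is not.

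**What to change.** - Prespecify the primary analysis as ANCOVA of 1-year PROMIS UE on arm and baseline PROMIS UE. Take the 95% confidence interval for the adjusted difference from that model and compare it with the 9.0-point margin.
- Keep N at 68. Because r is unknown, the gain should serve as a reserve against a larger SD or a small true disadvantage, and not be used to cut recruitment.
- Analyse each continuous secondary outcome that has a baseline value in the same way, adjusted for its own baseline. This also settles the ambiguous wording on mean differences.
- Remove the baseline significance tests and keep the descriptive table.

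The cost is one degree of freedom in each model and a change of wording. No visit, questionnaire or patient is added. The change should be made before any outcome data are compared by arm.
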